**Figure 3 figure3:**
[figure not shown]
Consort of the project. A_1c_: glycemic control; BDI: Beck Depression Inventory; BPI: Brief Pain Inventory; CBT-I: cognitive behavioral therapy for insomnia; DCP: diabetic care profile 
DSCB: diabetes self-care behavior; ESS: Epworth Sleepiness Scale; GAD-7: Generalized Anxiety Disorder–7; ISI: Insomnia Severity Index; PSQI: Pittsburgh Sleep Quality Index; and T2D: type 2 diabetes.

#### Sample Size

To detect the effect of CBT-I on people with T2D and symptoms of insomnia, the change in pre-post ISI was used to determine sample size. Pre-post changes using the minimal clinically meaningful difference of 8 points for the ISI in a previous study [124] were used to estimate the effect size. This calculation resulted in 10 participants per group to reject the null hypothesis of equal means when the population mean difference equals 8 with a standard deviation of 7. We accounted for an expected attrition rate of 40%, which indicated 28 subjects in both groups to detect the significant difference between groups after allowing for attrition at a .05 significant level and power of .80.

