##### Statistical Methods

A chi-square test will be used to compare between-group differences in categorical variables. Independent 2-sample *t* tests will be used to compare differences in continuous between-group demographic characteristics and clinical variables.

For the main analysis**,** the effect of the CBT-I intervention will be investigated by calculating change scores for the insomnia severity; DSCB; A_1c_; fatigue; sleep quality; daytime sleepiness; and symptoms of depression, anxiety, and pain. In addition, for variability of each sleep outcomes (SE, SL, TST, and WASO), CV of 7 nights before the pre- and postintervention assessments will be calculated, and change scores will be calculated. Then, independent sample *t* tests will be utilized to investigate the between-group difference in the change score means of all outcomes. A completer vs noncompleter analysis will be performed. For all analyses, alpha level will be set at .05.

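### The 10 completers per group behind the .80 power claim match only an undeclared one-sided .05 test; a two-sided test has about 68% power, and .80 after 40% attrition fails on either reading

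*Protocol article*

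**What the plan says.** The Sample Size section bases the calculation on the primary outcome: "the change in pre-post ISI was used to determine sample size". Its difference and result are: "This calculation resulted in 10 participants per group to reject the null hypothesis of equal means when the population mean difference equals 8". The SD used is 7. The section then allows for 40% attrition, arrives at 28 participants in total, and says this number is enough "to detect the significant difference between groups after allowing for attrition at a .05 significant level and power of .80".

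Statistical Methods fixes the test. Change scores are formed, and independent-sample t tests "will be utilized to investigate the between-group difference in the change score means of all outcomes". Alpha is .05 for all analyses. Trial Design gives 1:1 allocation, and Allocation Sequence Generation gives 14 participants per arm.

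Neither these sections nor the Abstract says whether the .05 is one-sided or two-sided. Objectives and Hypotheses words the hypothesis in the direction of benefit from CBT-I, and Trial Design refers to a superiority framework. Neither statement declares a one-sided test. The Sample Size section also does not say whether the SD of 7 belongs to the change score or to a single ISI score.

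**The concern.** A standardised difference of 8/7 = 1.14 is large, but with the usual two-sided t test 10 per group is too few for 80% power. The stated null is equality of means and the alpha carries no qualification, so most readers will assume a two-sided test. They will then credit the design with a power that its own inputs do not give.

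This matters because ISI is the only outcome the trial is powered on, as the Limitations section confirms. If 10 per group complete and the test is two-sided, a true 8-point benefit would be missed about 32% of the time, not the 20% implied. The attrition allowance is affected as well. The 28 enrolled are presented as 20 completers plus a reserve, but under a two-sided test 28 is the number needed with no dropout.

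**Working it through.** **Inputs** (Sample Size, Statistical Methods, Trial Design, Allocation Sequence Generation): difference Δ = 8; SD = 7, taken as the SD of the change score; alpha = .05; target power .80; 1:1 allocation; independent t test; 10 completers per group; 14 randomised per group; attrition 40%.

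**Step 1: reproduce the figure of 10.** Normal approximation: n per group = 2 × (z_alpha + z_power)² × (SD/Δ)².

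- One-sided .05: 2 × (1.645 + 0.842)² × (7/8)² = 9.47, rounded up to 10. This matches the article.
- Two-sided .05: 2 × (1.960 + 0.842)² × (7/8)² = 12.02, rounded up to 13. This does not match.
- A paired (one-sample) two-sided test with n = 10 has 89.4% power, so a within-group calculation does not explain the figure either.

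**Step 2: exact power of the planned test.** For group sizes n1 and n2, the t statistic has n1 + n2 − 2 degrees of freedom and noncentrality Δ / (SD × √(1/n1 + 1/n2)). At 10 per group this is (8/7) × √(10/2) = 2.556 with 18 degrees of freedom. Power from the noncentral t distribution:

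| Completers | Two-sided .05 | One-sided .05 |
|---|---|---|
| 8 + 8 | 56.7% | 70.1% |
| 9 + 8 | 59.5% | 72.5% |
| 10 + 10 | 67.6% | 79.2% |
| 11 + 11 | 72.2% | 82.7% |
| 13 + 13 | 79.8% | 88.2% |
| 14 + 14 | 82.9% | 90.3% |

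At least 80% needs 14 per group two-sided and, strictly, 11 one-sided. The one-sided shortfall at 10 is under one percentage point and is not worth pressing.

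**Step 3: what 10 per group could detect two-sided.** 80% power would need a true difference of about 9.3 points with SD 7, or an SD of about 6.04 with a difference of 8.

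**Step 4: the attrition allowance.** The total of 28 equals 20 × 1.4. Losing 40% of 28 leaves 28 × 0.6 = 16.8, about 17 completers, or 8 to 9 per group. This is below the 20 that the calculation itself requires. Keeping 20 completers after 40% loss would take 10/(1 − 0.40) = 16.7, so 17 per group or 34 in total. The first two rows of the table give the power at the expected attrition: 57% to 59% two-sided and 70% to 73% one-sided.

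**Step 5: sensitivity to the meaning of the SD.** If 7 were the SD of a single score, the SD of the change would be 7 × √(2(1 − r)), where r is the pre-post correlation. The article gives no r, so this is an assumption. At r = 0.5 the change SD is again 7. At about r = 0.63 it is 6.04, and 10 per group would reach 80% two-sided. Below r = 0.5 power is lower than in the table.

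**The case against.** The strongest reply is that the arithmetic may be sound. A one-sided .05 calculation gives exactly 10, the hypothesis is directional and the framework is superiority, so an undeclared one-sided calculation is a likely explanation. This stands to the extent that a reader might infer that the base sample size is simply miscalculated, and the article does not support that. What it supports is that the figure fits only a test that is nowhere declared, while an unqualified .05 against a null of equal means is conventionally read as two-sided.

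A reader might also infer that the trial has 68% power even with full retention. That is not so. With all 28 retained, the 14 per group give 82.9% two-sided. The 68% applies when exactly 10 per group remain. Nor is there strictly no margin, because losing one participant per group leaves 79.8%, practically the target.

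Three further points have some weight. Participant Timeline asks those who withdraw during the intervention to attend reassessment, so stopping treatment need not mean a missing ISI score; how many would return is unknown. The meaning of the SD is open, although the sentence about pre-post change points to the change score. Finally, this is a pilot with recruitment complete, and the Discussion says more research will be needed to verify its findings, so misreading a null result is a risk rather than something the article proposes. None of this rescues the claim of .80 power after 40% loss.

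**Conclusion.** The point holds in this form. Ten completers per group deliver the stated power only under a one-sided .05 test that the article does not declare. Under the conventional two-sided t test the power is 67.6%, about 12 percentage points below the claim, and 14 per group are needed. The 14 per group randomised reach 82.9% two-sided with full retention. At the attrition the article itself expects, power is about 59% two-sided or 73% one-sided at best, so the claim "after allowing for attrition at a .05 significant level and power of .80" is not met on either reading.

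These figures assume that 7 is the SD of the change score in both groups, that the true difference is 8, and that attrition removes participants from the ISI analysis and is spread roughly evenly between arms.

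**What to change.** 1. State in both Sample Size and Statistical Methods whether the .05 test is one-sided or two-sided, and confirm that 7 is the SD of the ISI change score.
2. If two-sided, replace 10 with 14 per group as the number needed for .80, and report about 68% power at 10 completers per group and about 83% at 14.
3. If one-sided, declare it in both sections, so that the analysis matches the calculation.
4. In either case, withdraw the claim of .80 power after 40% attrition or replace it with the power at the expected number of completers: about 59% two-sided or 73% one-sided with 17.
5. Say that a non-significant ISI result will be interpreted through its confidence interval, by whether that interval excludes an 8-point benefit.

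These are wording changes. Recruitment is complete and no further enrolment or procedure is required. The cost is a less favourable power statement.

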### Objectives and Hypotheses

The primary objective of this study is to establish a protocol for a pilot study to (1) investigate the effect of 6 sessions of CBT-I on insomnia severity in people with T2D and insomnia symptoms and (2) explore the effect of 6 sessions of CBT-I on sleep variability; fatigue; A_1c_; DSCB; sleep quality; daytime sleepiness; and the severity of depression, anxiety, and pain in people with T2D and insomnia symptoms. We hypothesized that people in the CBT-I group will have greater improvement in insomnia severity, sleep variability, fatigue, A_1c_, DSCB, sleep quality, daytime sleepiness, and severity of depression, anxiety, and pain compared with people receiving only health education (HE). We anticipate the improvement in insomnia severity will positively impact people with T2D and health outcomes because of the relationship between insomnia symptoms and diabetes-related health outcomes.

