## Methods

### Trial Design

The study design will be a pilot randomized controlled trial (RCT). This study will have an allocation ratio of 1:1, and this pilot RCT will be using a superiority framework to test the effectiveness of the experimental CBT-I intervention. This protocol is in accord with the Standard Protocol Items: Recommendations for Interventional Trials 2013 statement [65], and the intervention will be described according to the Consolidated Standards of Reporting Trials 2010 guideline [66].

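### The sample size of 10 per group for 80% power matches only a one-sided .05 test, which the protocol never declares; if the t test is two-sided, power is about 68%.

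*Protocol article*

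**What the plan says.** The Sample Size section of the protocol article bases the calculation on the Insomnia Severity Index (ISI), the primary outcome. It takes its target from "Pre-post changes using the minimal clinically meaningful difference of 8 points for the ISI in a previous study" and reports that this led to "10 participants per group to reject the null hypothesis of equal means when the population mean difference equals 8 with a standard deviation of 7". It then allows for 40% attrition, arrives at 28 participants in total, and closes with the operating characteristics "at a .05 significant level and power of .80".

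Statistical Methods compares change-score means between the groups with independent-sample t tests and adds: "For all analyses, alpha level will be set at .05". Trial Design says "This study will have an allocation ratio of 1:1" and describes the trial as "using a superiority framework to test the effectiveness of the experimental CBT-I intervention". Allocation Sequence Generation gives 14 participants to each arm.

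None of these sections says whether the .05 is one- or two-sided. The nearest statement is the directional hypothesis under Objectives and Hypotheses: "We hypothesized that people in the CBT-I group will have greater improvement in insomnia severity".

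**The concern.** The article gives a difference, a standard deviation, an alpha, a power, a test and a resulting number per group. These should fit together. With the most common reading of an unqualified .05, a two-sided test, they do not: 10 per group is too few for 80% power. They fit only if the calculation was one-sided, and the reader is not told that.

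The stated power describes the primary comparison, and the Limitations section says that the study is powered on the ISI. If the analysis is two-sided while the sample size was one-sided, the chance of missing a true 8-point effect with 10 per group is about one in three (1 − 0.676 = 0.324), not the one in five that the text implies. A reader weighing a non-significant result needs the right figure.

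**Working it through.** **Inputs, all from the protocol article**
- Difference 8 and standard deviation 7 (Sample Size), so d = 8/7 = 1.143.
- Alpha .05 (Sample Size and Statistical Methods); sidedness not given.
- Target power .80 (Sample Size).
- 1:1 allocation (Trial Design).
- Independent-samples t test on change scores (Statistical Methods).

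**Step 1: reproduce the stated 10 per group.** The normal approximation is n per group = 2 × [SD × (z_alpha + z_power) / difference]². Here 2 × (7/8)² = 1.53125.
- One-sided .05: 1.53125 × (1.645 + 0.842)² = 9.47, rounded up to **10**. This is the plan's figure.
- Two-sided .05: 1.53125 × (1.960 + 0.842)² = 12.02, rounded up to 13.

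So the stated number is reproduced, but only one-sided.

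**Step 2: exact power of the planned t test.** With n per group, the test statistic follows a noncentral t distribution with 2n − 2 degrees of freedom and noncentrality d × √(n/2). At n = 10 that is 18 degrees of freedom and 1.143 × √5 = 2.556. The critical value is 2.101 two-sided and 1.734 one-sided.

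| Evaluable per group | Power, two-sided .05 | Power, one-sided .05 |
|---|---|---|
| 8 | 0.567 | 0.701 |
| 10 | 0.676 | 0.792 |
| 11 | 0.722 | 0.827 |
| 13 | 0.798 | 0.882 |
| 14 | 0.829 | 0.903 |

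Two-sided, 13 per group falls just short of 80%, and 14 is the first number to reach it. One-sided, 10 per group gives 79%, which differs from .80 only by the rounding of the normal approximation.

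**Step 3: could another reading give 10 two-sided?** With a difference of 8 and 10 per group, two-sided power reaches 80% only if the SD is about 6.0 (power 0.805), not 7. A paired, single-group two-sided t test with the same inputs already gives 0.850 at 9 participants and 0.894 at 10, so it does not explain 10 per group at 80% either.

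**Step 4: what the plan's own attrition leaves.** 28 × (1 − 0.40) = 16.8 evaluable, or 8.4 per group. At 8 per group, power is 57% two-sided or 70% one-sided. To end with 14 evaluable per group under 40% loss, 14 / 0.60 = 23.3, so 24 per group or 48 in total would have to be enrolled. Fourteen evaluable therefore cannot stand beside 28 enrolled unless nobody is lost.

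**The case against.** The strongest reply is that the calculation is not wrong. The hypothesis is directional, the trial has a superiority framework, and a one-sided .05 calculation returns exactly 10. This stands as far as it goes. A reader might infer from the 68% that the sample size is a plain arithmetic error, or that 10 per group cannot give 80% power. The document does not support that, because it never says that the test is two-sided. A null hypothesis of equal means does not settle the matter, since that wording is used with either kind of test.

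The reply does not remove the problem. A directional hypothesis in a superiority trial does not make the test one-sided. One alpha of .05 is set for all analyses, including the baseline comparisons, for which no direction is hypothesised, and no switch to one-sided testing is announced for the outcomes. The figures agree only under an assumption that the text leaves out.

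A second stronger reading concerns the 8 points, which the article describes as a pre-post meaningful change but uses as the difference between arms. A reader might infer that the plan wrongly assumes no improvement under health education. The documents do not establish this. Eight points is declared as the population mean difference to be detected, and a meaningful difference may be chosen as a design target. The Introduction says that sleep hygiene is ineffective on its own, and the control arm's brief version leaves out the consistent sleep schedule and the association of bed with sleep. No figure for improvement in the control arm is given. As pure assumptions, between-arm differences of 6 or 4 points would give power at 10 per group of 0.44 or 0.23 two-sided (0.58 or 0.34 one-sided). These are illustrations, not evidence of an error.

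It is also fair to say that this is a labelled pilot with recruitment complete, and that the Discussion asks for more research to verify its findings. That limits the consequences, but the stated power should still be correct.

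**Conclusion.** The point holds in conditional form. The Sample Size section claims power .80 without stating sidedness, and its 10 per group is consistent only with a one-sided .05 test. If the primary t test is two-sided, as an unqualified .05 is usually read, power at 10 evaluable per group is about 68%, roughly 12 percentage points below the claim (80 − 67.6 = 12.4), and 80% would need 14 evaluable per group. If the expected 40% attrition occurs, about 8 per group remain, and power is about 57% two-sided or 70% one-sided. The 83% two-sided figure applies only if all 14 per group are evaluable.

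These results take the article's own difference of 8 and SD of 7 as given, with equal group sizes and an unadjusted t test. The one input that the article does not supply is sidedness, and both possibilities are shown.

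**What to change.** State in both Sample Size and Statistical Methods whether the primary test is one- or two-sided.

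- **If two-sided:** keep the 28 enrolled. Replace the power claim with about 68% at 10 evaluable per group, about 57% at the roughly 8 per group left after 40% attrition, and 83% only if all 14 per group are evaluable.
- **If one-sided:** declare it, justify it, and give power of about 79% at 10 and about 70% at 8 per group.

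Do not write 14 evaluable per group beside 28 enrolled, because with 40% expected attrition the two contradict each other.

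Optionally, add a sentence saying that the 8 points is described as a pre-post meaningful change and is used here as the between-arm difference. Label any power figures for smaller differences as assumptions.

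The cost is a change of wording, with no added enrolment. The downside is that the stated power becomes less favourable.

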### Assignment of Interventions (for Controlled Trials)

#### Allocation Sequence Generation

We will use random mixed block size randomization [125] to assign participants to either CBT-I (n=14) or HE (n=14) groups. Participants will be stratified by age where 62 years is the value that will stratify participants into either the older (63-75 years) or the younger (40-62 years) age group. The reason we chose age as a blocking variable is that the impact of age on sleep is more pronounced than gender [126], as older adults often have poorer [127] and lower slow wave [128] sleep, as compared with young adults.

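### 28 randomised with 40% attrition leaves about 17 completers, not the 20 the sample size calculation requires, so the stated .80 power is not delivered

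*Protocol article*

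**What the plan says.** All the inputs and the result are printed in the Sample Size section of the protocol article.

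- Evaluable requirement: "This calculation resulted in 10 participants per group to reject the null hypothesis of equal means", which is 20 in total.
- Effect and spread on the Insomnia Severity Index (ISI): "when the population mean difference equals 8 with a standard deviation of 7".
- Attrition and resulting total: "We accounted for an expected attrition rate of 40%, which indicated 28 subjects in both groups to detect the significant difference between groups".
- What the total is said to achieve: detection of the difference "after allowing for attrition at a .05 significant level and power of .80".

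The total of 28 is used consistently elsewhere. Allocation Sequence Generation plans "to assign participants to either CBT-I (n=14) or HE (n=14) groups", in line with the 1:1 ratio under Trial Design. The abstract and the Results section also give 28. The 40% is described only as an expected attrition rate and is not redefined anywhere.

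**The concern.** An attrition allowance should make the number left after dropout equal to the number the power calculation needs. Here the number randomised exceeds the requirement by 40% of the requirement (8 added to 20), whereas the expected loss is 40% of those randomised (11.2 of 28). The two are not the same, and the difference works against the trial.

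At stake is the truth of the power statement. Although the trial is called a pilot, the article adopts a superiority framework, names insomnia severity as primary, tests it at .05, and says under Limitations that the study is powered on the ISI. A reader would therefore judge a non-significant ISI result against a stated .80 power that the plan's own attrition figure contradicts. Later trials might also copy the inflation method.

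**Working it through.** **Inputs (Sample Size section unless noted).** Requirement 10 per group, 20 in total; difference 8; SD 7; attrition 0.40; alpha .05; target power .80; total 28, as 14 + 14 (Allocation Sequence Generation); independent two-sample t test on change scores (Statistical Methods). Sidedness is not stated: Statistical Methods says only "For all analyses, alpha level will be set at .05". Both readings are shown.

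**1. Reproducing the plan's total.**
- Multiplying: 20 × (1 + 0.40) = 28, an exact match (per arm 10 × 1.4 = 14).
- Dividing: 20 / (1 − 0.40) = 33.3, rounded up to 34 (per arm 10 / 0.6 = 16.7, so 17).

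The article does not print the formula, so the multiplication is inferred from the exact match. The next step does not depend on it.

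**2. What 28 leaves.**
- Completers at 40% loss: 28 × 0.60 = 16.8, or 14 × 0.60 = 8.4 per arm.
- Shortfall against 20: 3.2, about 3 participants.
- Largest loss that still leaves 20: 28 − 20 = 8, and 8 / 28 = 28.6%.

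**3. The base figure of 10 per group.** With the normal approximation, n per group = 2 × [SD × (z for alpha + z for power) / difference]².
- One-sided .05: 2 × [7 × (1.645 + 0.842) / 8]² = 9.47, so 10. This matches.
- Two-sided .05: 2 × [7 × (1.960 + 0.842) / 8]² = 12.02, so 13. This does not match; the t-test solution is 13.05, so 14.

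The plan's 10 per group is thus recovered only on a one-sided reading. That is a separate issue, but it determines how much of the power shortfall belongs to attrition.

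**4. Power of the t test.** Standardised difference 8 / 7 = 1.143. Noncentrality = 1.143 × √[n₁n₂ / (n₁ + n₂)], with n₁ + n₂ − 2 degrees of freedom.

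| Completers per arm | One-sided .05 | Two-sided .05 |
|---|---|---|
| 10 and 10 (plan's requirement) | 0.79 | 0.68 |
| 8 and 9 | 0.73 | 0.59 |
| 8 and 8 | 0.70 | 0.57 |

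**5. The part due to attrition.** Falling from 10 per arm to 8 or 9 costs about 7 to 9 percentage points one-sided (0.79 to 0.73–0.70) and about 8 to 11 two-sided (0.68 to 0.59–0.57). The rest of the two-sided gap, from .80 to 0.68, comes from the base figure.

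**6. Both corrections together.** With 14 evaluable per arm for a two-sided t test and 40% loss, 28 / 0.6 = 46.7, so 47, or 48 with equal arms.

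**The case against.** The arithmetic itself is hard to dispute, so the objections concern attribution and weight.

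*Two issues are mixed in the two-sided figures.* This is fair. Setting 0.57–0.59 against .80 overstates what the attrition step alone does, because 10 per arm already gives only 0.68 two-sided. The isolated loss is 7 to 11 points, depending on sidedness. The .80 claim still fails on the one-sided reading, which is the one that favours the plan.

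*The multiplication is an inference.* This is also fair, since no formula is shown. The conflict among 10 per group, 40% and 28 exists however 28 was obtained.

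*Attrition need not mean a missing outcome.* Participant Timeline says that those who withdraw during the intervention will be asked to complete the reassessment, so loss of the ISI endpoint could be below 40%. That is only a request, and the Sample Size section makes no use of it: the 40% is the loss it claims to have allowed for.

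*It is a pilot whose recruitment is complete.* This is true, and the error changes neither the test nor the allocation. It limits the remedy to a restatement but does not make the printed power claim correct.

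**Conclusion.** The concern holds. On the plan's own figures, 28 randomised with 40% attrition yields about 17 completers, not 20; 34 would have been needed to keep 20. Expected power for an 8-point difference with SD 7 is about 0.70 to 0.73 one-sided, or 0.57 to 0.59 two-sided, against the stated .80.

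These results take the 40% as loss of the primary outcome, spread about evenly over the arms, and take the difference and SD as given. The figure of 34 corrects the attrition step only and accepts 10 per group, which the stated inputs support only for a one-sided .05 test.

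**What to change.** Withdraw the claim of .80 power after attrition and replace the sentence with wording such as:

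> *Twenty-eight participants are randomised. With 40% attrition about 17 would be evaluable (8 or 9 per group), giving power of about 57–59% (two-sided .05) for an 8-point difference with SD 7. The 20 evaluable participants in the calculation are retained only if no more than 8 of 28 (28.6%) are lost.*

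State the sidedness alongside it. If the test is meant to be one-sided, the matching figure is about 70–73%. Describing the ISI comparison as a pilot estimate with a 95% confidence interval would suit the expected precision and the study's own label.

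The cost is wording and a less favourable stated power. Recruitment was complete at 28 when the article appeared, and no further enrolment is asked for. The correction should be in place before the ISI result is interpreted.
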